
#### The e-predictD monitoring system

Once patients choose the PPP to be self-implemented in the next 3 months, a monitoring and support plan for each specific PPP is established. The DSS will add new decision algorithms based on the comparative information of the previous assessments. For example, if the risk level for depression has increased at 3 months from moderate to high and the DSS and the patient did not previously select the ‘working with thoughts’ intervention module of the PPP, this will be suggested in his/her new PPP. This decision is based on the available evidence on the hierarchy of mediators involved in the prevention of depression (42). The e-predictD monitoring system will send messages, brief reports, tracking charts, and alerts throughout the study (see Figure 8). If patients consent, their GPs will also have access to this monitoring information and will be able to check their patient's e-predictD report, completed assessments, and the modules in which their patients are working (PPP) at any time.

**Figure 8 F8:**
[figure not shown]
The e-predictD monitoring system. **(Screen A)** System regulation Notifications and monitoring by the app. **(Screen B)** Notifications for the patient regarding the content of the different modules active in the app. **(Screen C)** Alarms and reminders for the patient regarding evaluations or entries for the different modules that are active.

### The intervention for the control group

Patients of both arms will continue to receive CAU from their health providers. Patients assigned to the control group download an alternative version of the e-predictD app that looks very similar to the intervention group's version. They will receive brief messages about general health information and mental health in particular (active control group). This information will be sent weekly for 52 weeks through the e-predictD app and will be extracted from brochures, clinical practice guidelines, and official websites (e.g., WHO; see Figure 9). However, in the active control group, there will be no personalization, information on the level of risk, risk factors, or internal–external resources to prevent depression. Nor will there be interaction, PPPs, or an initial GP–patient interview. GPs in the control group will not receive any training. Patients of both intervention and active control groups will receive the same notification and reminders to complete the questionnaires during follow-up.

**Figure 9 F9:**
[figure not shown]
The e-predictD intervention for patients in the active-control group. **(Screen A)** Once a patient in the control group has completed the questionnaires, he/she does not receive a report. Instead, this informational message is sent to the patient. **(Screen B)** In the main menu of the control group app where the boxes with the messages they will receive are displayed, a total of 52 messages will be sent each week for the next 12 months. The messages are stored in these four blocks. **(Screen C)** Message sent to a patient in the control group. It also contains an evaluation question that the patient must answer.

### Safety protocol

In any trial concerned with mental health, there is the potential for psychological distress in participants. Patients in either arm falling into PHQ-9 or/and Generalized Anxiety Disorder (GAD-7) score above 14 and/or reporting suicidal ideation (“nearly every day” in item 9 of the PHQ-9) at baseline and/or during follow-up will be automatically informed regarding their mental health. Through sequential messages over time, they will be suggested to seek further help from their GPs. Additionally, an optional call-back service for individuals requiring further support or direction will be provided. This call-back will occur within 3 days by a staff psychologist who will guide participants into necessary care arrangements.

### Outcomes, variables, measurements, and follow-up

For an overview of instruments used at baseline and at 3-, 6-, 9-, and 12-month follow-up assessments, see Table 1.

#### Outcomes

Our primary outcome is the cumulative incidence of major depression during 12 months of follow-up, assessed through the depression section of the CIDI (68) at 6 and 12 months. As secondary outcomes, we will use measurements of mental and physical quality of life using the SF-12 (69), depressive and anxious symptoms [PHQ-9 (70) and GAD-7 (71)], and the probability of the onset of major depression at 12 months (predictD risk algorithm) (28). All of these will be evaluated at baseline and at 3, 6, 9, and 12 months. We will also make estimates of cost-effectiveness and cost-utility (see economic evaluation below).

#### Variables and measurements

The questionnaires and questions were self-completed online by patients at baseline and at 3, 6, 9, and 12 months; except for the assessment of PHQ-9 and the predictD risk algorithm at baseline. These were collected face-to-face by the research assistants in the screening and these data were automatically incorporated into the database through a web application, along with the rest of the self-completed measures at baseline.

- The Patient Health Questionnaire (PHQ-9) (70) includes nine items that evaluate the presence of depressive symptoms in the last 2 weeks. Each item has response options ranging from 0 to 3 (0 = “not at all,” 1 = “several days,” 2 = “more than half of the days” and 3 = “nearly every day”). The score range is 0–27. The PHQ-9 showed good psychometric properties in Spain (53).- The Generalized Anxiety Disorder questionnaire (GAD-7) (71) includes seven items measuring anxious symptoms in the last 2 weeks, which are based on the DSM diagnostic criteria for GAD. The GAD-7 is also an effective screener for panic, social anxiety, and post-traumatic stress disorders (72). Response options are similar to those of the PHQ-9, and the score ranges from 0 to 21. The Spanish version of the GAD-7 also had good psychometric properties (73).- The Spanish predictD risk algorithm calculates the individual probability of the onset of major depression in the next 12 months. The predictD-Spain algorithm has been internally validated in Spain and externally validated in Chile and other European countries, showing excellent calibration and discriminant validity (C-index 0.82) (28). The predictD-Spain risk algorithm outperformed the predictD-Europe risk algorithm by 5.6 Integrated Discrimination Improvement (IDI) points when used in Spanish primary care attendees (28). The predictD-Spain algorithm comprises a set of 11 predictors:

Spanish province.Age.Gender.Educational level (beyond secondary education, secondary education, primary education, or incomplete primary education/illiterate).Quality of life, using the SF-12 (69). This questionnaire consists of two components, one related to physical health and another related to mental health. The scores range from 0 to 100; higher scores indicate better health-related quality of life. The SF-12 was validated in the Spanish population and demonstrated adequate reliability and validity (74).Controls, demands, and rewards for unpaid work using an adapted seven-item version of the Job Content Instrument (75). This questionnaire consists of questions about difficulties in unpaid work, the frequency with which help is perceived, and satisfaction with this unpaid work. The result is classified into three categories (satisfied, dissatisfied, and very dissatisfied) through the sum of the seven items. This questionnaire showed good psychometric properties in Spain (76).Satisfaction with living together at home, using an option from the five-item Likert response scale ranging from 1 (very dissatisfied) to 5 (very satisfied).Presence of serious problems in relatives or close persons, using four different dichotomous response (yes/no) items on serious physical, psychological, and substance misuse problems and/or disability.Childhood experiences of physical abuse, using an option from the five-item Likert response scale ranging from 1 (never) to 5 (frequently).Screening for lifetime depression, using the first two questions included in the CIDI about lifetime low mood (77).Medication consumption for anxiety, depression, or stress, in the previous 6 months through an item with a dichotomous answer (yes/no).

- Two questions from the Spanish version of the Duke-UNC-11 instrument for evaluating perceived functional social support, one referring to affective social support and another to confidential social support subscales. Both items have the highest item-subscale correlation. Each item has response options ranging from 1 (“much less than I wish”) to 5 (“as much as I wish”) (78).- Physical activity using a brief physical activity assessment (79, 80) consisting of two questions, one that assesses the frequency and duration of vigorous-intensity physical activity and another that assesses the frequency and duration of moderate-intensity physical activities (including walking) undertaken in a week. A score >4 = “sufficiently” and 0–3 = “insufficiently” active.- A question about whether the participants have difficulty saying ‘no’ to other people with four Likert response options ranging from 0 (never) to 5 (frequently).- A question about whether the participants have difficulty communicating with other people with four Likert response options ranging from 0 (never) to 5 (frequently).- A question about whether the participants have a conflict or problem with someone and they want to resolve it (yes/no).- A question about whether the participants have difficulties making decisions (yes/no).

The questionnaires hetero-administered by telephone at 6 and 12 months are the following:

- Depression section of the CIDI. The CIDI is a structured psychiatric interview that was designed and evaluated by the WHO (68), which has excellent reliability and validity in different cultures and populations (81, 82). Through the CIDI, we will obtain diagnoses of major depression based on DSM criteria.- To assess the attitudes and satisfaction of the patients regarding the e-predictD and the active control interventions, we use an adaptation of the e-Health Impact Questionnaire (e-HIQ) (83) selecting 17 of the 37 items included in the e-HIQ. This is hetero-administered at 6 and 12 months of follow-up. In addition, we have added an open-ended question to assess the appearance of adverse effects attributable to the e-predictD intervention or to the active control group: “In the last 6 months, have you noticed any discomfort related to the depression prevention intervention you are receiving? If so, please describe it in your own words.”

The questionnaires hetero-administered by telephone at baseline and at 6 and 12 months are the following:

- Healthcare resource use will be evaluated using the Client Service Receipt Inventory (56), which collects information on the use of services, psychotropic drugs, sick leave, and loss of productivity.- Quality-adjusted life years (QALYs) are measured using the EuroQol five dimension questionnaire (EQ-5D-3L) (84, 85). This is a widely used measure of general health and quality of life, which includes five domains that address mobility, self-care, usual activities, pain/discomfort, and anxiety/depression, and three answer options (no problems, some problems, and extreme problems). In addition, it includes a visual analog scale graded from 0 (the worst health status) to 100 (the best health status). Spanish tariffs will be used to estimate the utility of health states described by the patients (86).

The questionnaires and questions self-completed at baseline by the GP participants in both arms of the trial are the following:

- Spanish Province.- Primary care center (PCC)- Age.- Gender.- Job characteristics: urban or rural PCC, type of contract (permanent or temporary/substitute), months working at the current PCC, patient list size, and mean time per visit.- Training: year of medical degree earned, postgraduate training (3 or 4 years) in general and family medicine (yes/no), accreditation as a GP tutor (yes/no), experience in training GPs [first-year resident assigned (yes/no), and/or third- or fourth-year resident assigned (yes/no)], and membership in a Spanish health and communication group (yes/no).- Satisfaction with the management of patients with mental disorders in primary care: satisfaction with the communication and care shared with the mental health team (secondary care; five Likert response options), satisfaction with the role of the primary care nurse in mental health disorders (five Likert response options) and satisfaction with the role of the primary care social worker in psychiatric disorders (five Likert response options or “I do not have a social worker in my health center”).- Profile of professional practice: A three-dimensional questionnaire validated in Spain, with four items each and response options from 1 = “strongly agree” to 4 = “strongly disagree” concerning professional satisfaction, workload perception, and biomedical vs. psychosocial orientation (87).- Clinicians' attitudes toward depression will be evaluated using the Revised Depression Attitude Questionnaire. This questionnaire consists of 22 items on professional confidence in depression care, therapeutic optimism, and views on generalist or specialist perspectives pertinent to depression and its care (88, 89). The response options range from 1 (strongly disagree) to 5 (strongly agree) using a 5-point Likert scale.

#### Adherence

To improve study adherence, a research assistant will call participants when the following situations occur: (1) participants do not attend the interview with their GPs, (2) participants have not used the app (which means they have not entered any intervention module) after the visit with their GPs, and (3) participants have not self-completed any follow-up questionnaires.

### Data analysis

#### Power and sample size calculation

To calculate the necessary sample size, we estimate that in the control group, there will be an incidence of major depression of 20% in the year of follow-up since we have previously screened the patients at moderate-to-high risk for depression. We also expect that in the intervention group, the incidence of depression will be 11.2% (absolute risk difference = 8.8%; relative risk = 0.56). In the e-predictD study, we expect a greater effect size than in the predictD study because the latter implements a very simple intervention (a 15-min patient–GP interview every 6 months) for the universal prevention of depression; while in the former, the intervention is more intense and personalized and its target population is at a moderate-to-high risk. We assume an alpha error of 5% and a power of 80% for a two-sample Pearson's chi-squared (two-tailed proportion test) and cluster randomized design: 72 GPs (36 GPs for each group) and 10 patients per GP, assuming that the distribution of the cluster will be homogeneous (CV <0.23) (90), and an intracluster correlation coefficient for GPs of 0.04, which was obtained from a previous study (29). Therefore, we would need to recruit 720 patients in total, 360 for each arm of the trial.

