Even in the hypothetical situation where all cases of depression were correctly diagnosed and treated and patients were adherent, the disease burden of depression (YLDs) could only be reduced by 30% (16). This limitation occurs, among other reasons, because current treatments for depression are not as effective as we would like (17) and because of the so-called preventive gap. Approximately 40% of the 12-month prevalence of depression is due to the continuous occurrence of new cases of depression (10, 18). Therefore, an additional way to reduce the burden of depression is to lower the incidence of new cases, which can be achieved through prevention rather than treatment (19). We will use the term “interventions” to prevent depression only for those that were implemented before the onset of a depressive disorder (20). In the last two decades, dozens of systematic reviews and meta-analyses on psychological and psycho-educational interventions to prevent depression have been conducted (21). Nowadays, there is an agreement that psychological and psycho-educational interventions are effective, although their preventive effect is small, between 20 and 40% reduction in the incidence of depression compared to the control group (21, 22). From a public health point of view, this small effect size in relative terms could be clinically relevant in absolute terms (avoided depression, improvements in quality of life, and cost reduction) if preventive interventions were cost-effective (23) and scalable to a large number of people at risk. This could be achieved in the workplace (24), school settings (25), and primary care (26), and in a more transversal way, through information and communication technologies (ICTs) (27).

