Box 1Exclusion and inclusion criteria in the e-predictD study.Exclusion criteriaGPs will be excluded if they……are planning to change their place of work in the next 12 months.Patients will be excluded if they……are aged under 18 or over 55 years.…are unable to understand or speak Spanish.…have a documented severe mental disorder (psychosis, bipolar disorder, personality disorder…), cognitive impairment, or terminal illness.Inclusion criteriaPatients will be included if they……have a smartphone, tablet, or computer with an internet connection.… will maintain their place of residence in the respective cities for at least 9 months of the next year.…Obtain a baseline PHQ-9 score <10.…have a baseline probability of the onset of major depression at 12 months ≥10% according to the predictD risk algorithm.

Patients who had no exclusion criteria and met all inclusion criteria were informed in writing by the research assistants that two interventions (interventions A and B) would be tested to prevent depression, they would be randomly assigned to one of them, and that both interventions will be implemented online, through their smartphones or/and tablet-computers. Once the patient information and selection process was complete, the research assistants gave them the second consent form to be signed if they wanted to participate in the trial. If this last informed consent is signed, then the research assistants provided participants with the web address of the e-predictD app and an access code to download the app. In addition, the research assistants were available to help patients install the app on their smartphones if necessary.

We anticipated recruiting a total of 720 patients (10 for each of the 72 GPs) of which about 360, under the care of 36 GPs would be assigned to each of the two conditions (see below the “power and sample size calculation” section). Recruitment was affected by the COVID pandemic and only 69 GPs and 633 patients were recruited. The entire selection process for GPs and patients and the different evaluations over the 12-month follow-up are summarized in Figure 1.

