#### GP training and the GP–patient interview

Although the e-predictD is basically a self-guided intervention to prevent depression delivered through an app, we decided to hold a GP–patient interview because it was the main active ingredient of the predictD intervention (29–32), giving the GP a facilitator role within the e-predictD intervention. Nonetheless, in this case, we reduced the number of GP–patient interviews to just one per year, as the GPs suggested in the qualitative evaluation of this intervention (34). Another active ingredient of the predictD intervention that we decided to maintain in the e-predictD intervention was specific training for GPs, since most GPs have had no training in depression prevention and none in the new e-predictD intervention.

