(1) The GPs who choose to participate in the e-predictD study may have a different profile (psychosocial orientation, different training or work satisfaction, etc.) to those who do not. Similar biases could occur if a large proportion of patients refuse to participate. It is not easy to obtain information from those GPs and patients who refuse to participate, so it will be difficult to ascertain the direction and magnitude of this possible selection bias. (2) This potential selection bias could also limit external validity (98). In addition, the inferences of this trial will be limited to primary care attenders aged 18–55 years at moderate-to-high risk of depression with internet access and basic technological literacy. Nonetheless, primary care is an ideal setting to carry out primary prevention strategies for depression because many people at risk of depression go to see their GPs. (3) Apart from the only per protocol visit that patients will have with their GPs, the e-predictD is basically an intervention that is unguided and delivered via smartphone; therefore, trial attrition and disengagement are potential issues (99). Reasons for attrition are complex and, in reality, there are contradictory possibilities of drop-out due to dissatisfaction or lack of engagement, as opposed to drop-out due to a sense that the individual feels his/her needs have been met. We will use those evidence-based strategies to maximize engagement and adherence: reducing the length of follow-up questionnaires and giving participants feedback on their progress while filling out the questionnaire, automated tailoring, real-time engagement, gamification and intrinsic motivation to engage, log of past app use, reminders to engage, and a simple intuitive interface and interactions (100). To address the possibility that users may delete the app during the trial, which may hamper follow-up attempts, later follow-ups will occur via the phone numbers provided, rather than via the app. Participants will receive up to three phone calls to complete each assessment and follow-up measures will be accepted as long as they are obtained within 90 days of the planned assessment. In addition, we will use a robust statistical method (multiple imputations) for data missing at random, so we hope that this limitation will be minimized. (4) Although cluster randomization by GP will reduce possible contamination bias, some degree of contamination could occur due to the coexistence in the same PCC of GPs and patients of both control and intervention arms. The magnitude of this bias would be small, but in any case, it would go against the effectiveness hypotheses of the e-predictD study. (5) Since we evaluate a psychosocial intervention in real practice, it is not possible to blind GPs who provide it (55). Both the intervention and active control GP groups could modify their behavior because they feel observed (Hawthorne bias). These behavioral changes in the GPs in the active control group could be influenced by social desirability bias, whereby they could improve the usual care they provide to their patients in the control group; therefore, this last bias would also go against the hypothesis of this study. (6) We use an active control group, whose intervention (brief weekly psychoeducational messages) could have some preventive effect on depression, especially in those patients with a lower risk of depression, which could reduce the differences in the preventive effect between both the e-predictD and the active control groups. (7) The cluster randomization might produce a good balance between the groups at the GP level; however, this does not guarantee a good balance at the patient level (101), which could contribute to confounding bias. We will perform adjusted analyses for variables unbalanced at baseline if necessary. (8) Finally, there could be post-randomization biases (e.g., unbalanced use of antidepressants between the intervention and active control groups during follow-up), which will be addressed by carrying out measurements and adjusted analyses.

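### The 720-patient target delivers 80% power only if nobody is lost to follow-up, and the 80% is not restated for the 633 patients and 69 GPs recruited

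*Protocol article*

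**What the plan says.** The section on power and sample size in the protocol article sets out the whole calculation. For the control arm it assumes that "there will be an incidence of major depression of 20% in the year of follow-up", and for the intervention arm 11.2%, a difference of 8.8 points and a relative risk of 0.56. On error rates it says "We assume an alpha error of 5% and a power of 80"%, for a Pearson chi-squared comparison ("two-tailed proportion test) and cluster randomized design"). The clustering inputs are 72 GPs, 10 patients each, an intracluster correlation of 0.04 and a coefficient of variation of cluster size below 0.23. It concludes: "Therefore, we would need to recruit 720 patients in total, 360 for each arm of the trial". No loss to follow-up appears among the inputs.

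Two other places bear on this. The Patients section reports that, because of the pandemic, "only 69 GPs and 633 patients were recruited". The Discussion, limitation (3), says that because the intervention is essentially unguided and delivered by smartphone, "trial attrition and disengagement are potential issues". Neither place returns to the 80%.

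On effect size, the Introduction puts the preventive effect of psychological and psycho-educational interventions at "between 20 and 40% reduction in the incidence of depression compared to the control group" and reports a 21% reduction for the predecessor, the predictD intervention.

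**The concern.** A sample size formula returns the number of patients who must contribute an outcome. If that number is written down as the number to recruit, any loss takes the trial below its stated power. Here the shortfall in recruitment comes on top, and the article was published after recruitment had closed (the Design section gives the status as active, not recruiting), so the reduced sample was known when the 80% was printed.

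What is at stake is how a non-significant primary result is read. A reader who relies on the sample size section will treat it as evidence from a trial with an 80% chance of detecting the assumed effect. That effect, a 44% relative reduction, also lies just beyond the strong end of the range cited in the Introduction, so power for effects inside that range is lower still. The article itself says, at the end of the Discussion, that a relatively small preventive effect would be relevant.

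**Working it through.** **Inputs.** From the power section: p1 = 0.20, p2 = 0.112, two-sided alpha 0.05, power 0.80, ICC 0.04, m = 10 per GP, 36 GPs per arm, CV below 0.23 (0.23 used as the upper bound). From the Patients section: 633 patients and 69 GPs. From the Design section: 1:1 allocation. Loss rates are my assumption, since the article gives none.

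**Step 1: reproduce the plan's figure.** Pooled-variance formula for two proportions, with p̄ = 0.156:

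n = [1.96·√(2·p̄(1−p̄)) + 0.842·√(p1(1−p1)+p2(1−p2))]² / (p1−p2)²

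= [1.96·√0.26333 + 0.842·√0.25946]² / 0.088² = (1.0058 + 0.4287)² / 0.007744 = 265.7 per arm.

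Design effect = 1 + (10 − 1)·0.04 = 1.36. Then 265.7 × 1.36 = 361 per arm, against 360 stated. The plan's number reproduces, and it leaves nothing over for loss.

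**Step 2: power at the planned size with no loss.** Effective n per arm = 360/1.36 = 264.7, giving 79.9%. With CV 0.23 the design effect is 1 + ((1 + 0.23²)·10 − 1)·0.04 = 1.381, and power is 79.2%.

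**Step 3: the planned 720 with loss.** With equal cluster sizes, an assumed 10% loss gives 76.8% and 20% loss gives 73.1%. So the missing allowance is a feature of the design and does not depend on the recruitment shortfall.

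**Step 4: the recruited sample.** For N analysed patients, m = N/69, design effect = 1 + ((1 + 0.23²)·m − 1)·0.04, and effective n per arm = (N/2)/design effect. With no loss: m = 633/69 = 9.17, design effect 1.346, effective n = 316.5/1.346 = 235. The last column is the intervention incidence that would give 80% power against 20%.

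| Loss (assumed) | N analysed | Design effect | Effective n per arm | Power at RR 0.56 | Detectable at 80% power |
|---|---|---|---|---|---|
| 0% | 633 | 1.346 | 235 | 75.0% | 10.7% (9.3 points, RR 0.54) |
| 10% | 570 | 1.308 | 218 | 71.7% | 10.4% (9.6 points, RR 0.52) |
| 20% | 506 | 1.269 | 200 | 67.9% | 10.0% (10.0 points, RR 0.50) |
| 30% | 443 | 1.231 | 180 | 63.4% | 9.6% (10.4 points, RR 0.48) |
| 40% | 380 | 1.192 | 159 | 58.2% | 9.0% (11.0 points, RR 0.45) |

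With equal cluster sizes the power figures are at most 0.6 points higher (75.6% with no loss).

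**Step 5: effects inside the article's own evidence range.** At 633/69 with no loss and control incidence 20%, power is about 66% for RR 0.60 (the 40% end of the cited range) and about 22% for RR 0.79 (the predictD effect). With 20% loss these fall to about 59% and 19%.

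**The case against.** The best defence is that patients lost from the app are not all lost to the primary analysis. The diagnostic interview (CIDI) is done by telephone, with up to three calls and a 90-day window. The outcome is cumulative and is assessed at both 6 and 12 months, so a patient who becomes a case by month 6 already counts. Missing values are to be imputed, with repeated PHQ-9 scores available to inform the imputation, and the primary analysis adjusts for baseline risk, which the plan calls strongly predictive. The table above treats each lost patient as contributing nothing and uses an unadjusted test. All of this stands as a reason to read the figures as conditional on a simpler analysis. It does not rescue the stated 80%: the plan's own calculation is for a plain chi-squared test, claims no gain from adjustment or imputation, and gives no figures from which a gain could be worked out.

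It is also fair to say that the shortfall and its cause are openly disclosed, and that no stated number is miscalculated.

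Two stronger readings may tempt a reader.

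- One is that the trial simply has 58% to 75% power. The documents do not support that: 75% is the figure with no loss, 58% needs 40% loss, and no attrition rate is given anywhere.
- The other is that the relative risk of 0.56 is an error, since the article says of the GP–patient interview that "it was the main active ingredient of the predictD intervention" and then cuts it to one. The assumption is optimistic, but the plan gives reasons for it (a more intense and personalized intervention, and a population at moderate-to-high risk), and modules, updated plans and monitoring are added as interviews are reduced. Nor is the trial uninformative across the cited range: about 66% power at RR 0.60 with no loss is not negligible. Only the weak end, near RR 0.79, is poorly served.

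**Conclusion.** The point holds as a misstatement of power. The 720 is the number to be analysed, presented as the number to recruit, and the 80% does not describe the sample obtained. Recruitment alone costs about four points (79.2% to 75.0% at CV 0.23). Assumed losses of 10% to 30% take power to about 72% down to 63%.

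These figures rest on the plan's 20% control incidence, RR 0.56 and ICC 0.04, on CV at its upper bound, on an unadjusted test, and on lost patients carrying no information. The last two probably make the figures somewhat pessimistic, by an unknown amount. The direction is not in doubt for the calculation as the plan sets it out: at 633 patients its power is below 80% before anyone is lost.

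**What to change.** In the power section, or in a dated note to it:

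1. State that 720 assumed complete follow-up.
2. Replace the 80% with the power and the detectable difference at 633 patients and 69 GPs for the retention actually observed on the primary outcome, naming the test, ICC and CV used.
3. Add rows for effects inside the article's own evidence range, at least RR 0.60 and RR 0.79.
4. If credit is to be taken for baseline-risk adjustment or for imputation from the 6-month CIDI and PHQ-9, state the assumption behind it.

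The absolute risk difference is already the primary analysis, so nothing in the analysis has to change, and no extra enrolment is called for. The cost is a paragraph and a small table; the downside is a less favourable stated power.
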